## Abstract

**Introduction::**

Ulcerative colitis (UC) is a chronic inflammatory bowel disease (IBD) characterized by a relapsing-remitting course owing to recurrent intestinal inflammation. UC often has symptoms such as intermittent rectal bleeding, diarrhea, and abdominal pain. As the precise etiology of UC has not completely clarified, UC has become a public health challenge worldwide. According to an epidemiological survey, there were about 350,000 new cases of IBD in China from 2005 to 2014. By 2025, the number of IBD patients in China will reach 1.5 million. Traditional Chinese medicine (TCM) has been widely used to treat UC in China, however, it is still challenging to systematically determine the efficacy of in UC. Therefore, this trial aims to evaluate the clinical efficacy and safety of CHM in the treatment of mild active UC patients.

**Methods::**

A multi-center, double-blinding, double-dummy, active-controlled, randomized trial will be established. A total of 240 patients in 6 centers with mild active UC (Mayo score is 3–5 points) and TCM syndrome of damp-heat stasis blocking and spleen-qi deficiency will be randomly allocated in the ratio of 1:1 to 2 groups: the experimental group and the control group. The experimental group will receive Hudi enteric-coated capsules (HEC) and enteric-coated mesalazine tablets placebo; the control group will receive enteric-coated mesalazine tablets and HEC placebo. Each group will be treated for 8 weeks. The primary therapeutic outcome: the rate of clinical efficacy and clinical remission at 8 weeks of treatment (last survey point) according to the modified Mayo score. The secondary outcomes: individual symptom score, TCM syndrome score, endoscopic response rate, mucosal healing rate, and quality of life scale score. Outcomes will be assessed at baseline and the end of the trial. Besides, intestinal mucosa, stools and blood biopsies from the mild active UC patients before and after treatment will be collected to reveal the underlying mechanisms.

**Discussion::**

The results of this trial will provide compelling evidence of the efficacy and safety of HEC for treatment of mild active UC and preliminarily show the potential mechanism of how HEC acts. Finally, it will widen treatment options for patients with mild active UC.

## Introduction

1

Ulcerative colitis (UC) is a kind of inflammatory bowel diseases (IBD) characterized by chronic nonspecific inflammatory colorectal disease with a yet-uncharacterized etiology. UC often has symptoms such as intermittent rectal bleeding, diarrhea, and abdominal pain. It mainly affects young and middle-aged people between 18 and 50 years old.^[1]^ UC-related colorectal cancer accounts for 9% to 11% of the death causes of UC patients.^[2]^ UC was mainly prevalent in developed countries of Europe and North America. Studies have reported that the annual incidence of UC varies from 8.8 to 23.14 per 100,000 person-years in North America, 1.7 to 57.9 per 100,000 person-years in Europe, and prevalence was 139.8 to 286.3 per 100,000, and 2.42 to 412.0 per 100,000, respectively.^[3]^ According to an epidemiological survey, there were about 350,000 new cases of IBD in China from 2005 to 2014, and by 2025, the amount of IBD patients in China will reach 1.5 million.^[4]^ As the precise etiology of UC has not completely clarified, UC has become a public health challenge worldwide,^[5]^ and because of the widespread of the mild active period, our trail will focus on this specific type.

UC is treated with 5-aminosalycilate acid (5-ASA), corticosteroids, immune suppressants, and biological agents currently, especially, 5-ASA is recommended as a first-line therapy for mild-to-moderate UC patients.^[6]^ But those medicine often result in different adverse effects, a low response rate and a high risk of infection,^[5]^ however, complementary and alternative medicine (CAM), like traditional Chinese medicine (TCM), with lower adverse effects were used seldom in UC. TCM is one of the most commonly used modality for UC patients, accounting for 19% to 54% of CAM users,^[7]^ that is been known as useful in improving symptoms, reducing medical expenses and clinical evaluation for UC patients, but it is still challenging to systematically determine the efficacy of TCM in treatment.^[8]^

Numerous studies based on UC mouse models and clinical trials, especially randomized double-blinding clinical trials, remains the gold standard for evaluating the efficacy of TCM.^[9]^ To obtain more conclusive results on the risk-benefit ratio of TCM for UC, it is necessary to design and conduct a high-quality clinical trial with appropriate blinding method and a large number of patients. Hudi enteric-coated capsules (HEC) has finished a multi-center clinic randomized controlled trial in China,^[10]^ it confirmed that HEC played a pivotal role in treating mild to moderate UC by relieving symptoms effectively, but as the shortage of colonoscopy examination and treatment time, this trial was not rigorous enough. Besides, the mechanism of HEC in treating UC was not clear.

Therefore, the primary aim of this multi-center, double-blinding, double-dummy, randomized controlled trial is to evaluate the clinical efficacy and safety of HEC in the treatment of mild active UC patients. Meanwhile, we want to reveal the underlying mechanism of HEC how to treat mild active UC by molecular biology technology from the clinic specimens.

## 2.Materials and methods

2

### Ethical approval and consent to participate

2.1

The study is conducted in accordance with the Declaration of Helsinki (Edinburgh 2000 version). The final protocol (Date: April 15, 2019) of this trial has been approved by the team leader unit, Research Ethical Committee of Jiangsu Province Hospital of Chinese Medicine (Version number: 2019NL-039-02). In addition, this trial has been registered in the Chinese Clinical Trial Registry (No. ChiCTR1900023158, registered May 14, 2019). Before the enrollment, all participants would sign written informed consents. If there will be any significant modification of the protocol, it should be reviewed by the research ethical committee and updated on the registry web (http://www.chictr.org.cn) in time. Each participating center has conducted ethical filing and has the ethical approval of the leader unit. All volunteers signed the informed consent form before the trial and details could be inquired in the registry web or the corresponding author.

### Trial design

2.2

This study is a multi-center, double-blind, double-dummy, randomized, parallel positive controlled trial. We adopted a noninferiority trial design and followed the Standardized Protocol Interventions: Recommendations for Interventional Trials (SPIRIT) 2013 Statement.^[11]^ The experimental group was treated with HEC and enteric-coated mesalazine tablets (EMT) placebo, while HEC placebo and EMT were used in the control group. A total of 240 patients diagnosed with mild active ulcerative colitis (MAUC) and TCM syndrome of damp-heat stasis blocking and spleen-qi deficiency in 6 clinical trial centers are eligible for enrolment. We will implement randomization with a 1:1 allocation ratio in the experimental group (n = 120) or the control group (n = 120), and each patient will undergo an 8-week treatment. The study flowchart is showed in Figure 1.

**Figure 1 F1:**
[figure not shown]
Flowchart of the trial design. TCM = traditional Chinese medicine, ALT = alanine aminotransferase, AST = aspartate aminotransferase, TBIL = total bilirubin, DBIL = direct bilirubin, γ-GT = γ-glutamyl transpeptidase, ALP = alkaline phosphatase, Scr = serum creatinine, BUN = blood urea nitrogen, HEC = Hudi enteric-coated capsules, EMT = enteric-coated mesalazine tablets.

### Number of Samples

2.3

Number of Samples was determined based on the calculation of noninferiority trial design. The efficacy rates of EMT ranges from 65% to 71%,^[12,13]^ and the average rate is about 68%. Our previous study found that the efficacy rates of HEC is 83.11% in treating MAUC. The sample size was calculated by the following formula: 

*U*α, *U*β is the corresponding *U* value of α, β. When α equaling to 0.05, β equaling to 0.1, *U*α (0.05) is 1.645, *U*β (0.2) is 0.842. *P*_1_ and *P*_2_ represent the efficacy rates of HEC and EMT. *P* equals to (*P*_1_ + *P*_2_) /2 × 100%. The certainty was set at 80%, considering 20% of sample lose. The sample number was set to 120 for each group, 240 in total, and 40 samples in each center.

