### Data analysis

3.7

Data analysis will be performed by professional statisticians and the main researchers using SPSS 22.0. Statistical analysis included the actual number of subjects selected, cases of shedding and rejection, demography and other baseline characteristics, patient compliance, efficacy and safety analysis. We used frequency tables or percentages for categorical variables, and mean ± standard deviation for continuous variables to describe the characteristics of patients in both groups. Categorical data will be analyzed by chi-square test or Fisher exact test to compare the differences between the 2 groups, while quantitative data with normal distribution will be analyzed by *t* test. If the data does not conform to the normal distribution or the uniformity of variance, Wilcoxon rank sum test or Wilcoxon signed test will be used to analyze them to compare the two groups. A two-sided *P-*value <.05 will be set as the significant level.

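### The sample-size paragraph gives two values for β and a one-sided α, but the analysis section sets a two-sided test; 240 patients match only one-sided 0.05 with 80% power

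*Protocol article*

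**What the plan says.** Section 2.3 (Number of Samples) of the protocol article makes these statements:

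- Error rates: "When α equaling to 0.05, β equaling to 0.1".
- The α deviate: "U*α (0.05) is 1.645".
- The β deviate, given in the same sentence as the error rates: "U*β (0.2) is 0.842".
- Control rate: the range for mesalazine (EMT) is 65% to 71%, and "the average rate is about 68" percent.
- Experimental rate: "Our previous study found that the efficacy rates of HEC is 83.11% in treating MAUC".
- Power in words, and loss: "The certainty was set at 80%, considering 20% of sample lose".
- Result: 120 per group, 240 in total.

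Sections 2.2 and 2.3 both call the design noninferiority, but the text gives no margin. The formula itself is missing from the text available.

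Section 3.7 (Data analysis) compares categorical outcomes between groups with a chi-square or Fisher test of difference. For a two-sided P, it says that a "value <.05 will be set as the significant level".

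**The concern.** There are two contradictions. First, β cannot be both 0.1 and 0.2. The label 0.1 means 90% power, while the deviate 0.842 and the 80% in words both mean β = 0.2. Second, 1.645 is the deviate for a one-sided test at 0.05, whereas a two-sided test at 0.05 uses 1.96. The sample size was therefore computed for a less demanding test than the one section 3.7 describes.

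A reader cannot tell whether the trial was planned for 90% power, for 80%, or for something lower under the stated analysis. That matters when a non-significant result has to be interpreted, because the planned chance of missing the assumed effect is one of the figures the reader would use.

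**Working it through.** **Inputs (section 2.3).** P1 = 0.8311 and P2 = 0.68, so the difference is 0.1511. The mean rate is P = (0.8311 + 0.68)/2 = 0.75555. The deviates are 1.645 and 0.842.

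**Reproducing 120.** The paragraph defines a mean P, which points to the pooled difference formula with no margin:

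n = 2P(1 − P)(Uα + Uβ)² / (P1 − P2)²

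= 2 × 0.75555 × 0.24445 × (1.645 + 0.842)² / 0.1511² = 100.07 per arm.

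100.07 × 1.2 = 120.08, which matches 120. Dividing by 0.8 instead gives 125.09, or 126 per arm. Neither the 100 nor the 1.2 is printed, so the inflation step is an inference. An unpooled version gives 97 per arm, and 122 after dividing by 0.8, which is also close to 120.

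**What other readings of α and β would need (same formula).**

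| α and power | Evaluable per arm | Divided by 0.8 |
|---|---|---|
| One-sided 0.05, 80% | 100.1 | 126 |
| One-sided 0.05, 90% (Uβ = 1.282) | 138.6 | 174 |
| Two-sided 0.05, 80% (Uα = 1.96) | 127.0 | 159 |
| Two-sided 0.05, 90% | 170 | 213 |

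Among these margin-free readings, only the first leads to 120.

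**Power delivered for a test of difference.**

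Power = Φ{ [ (P1 − P2)√n − Uα√(2P(1 − P)) ] / √(P1(1 − P1) + P2(1 − P2)) }

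Here √(2P(1 − P)) = 0.6078, and the denominator is √(0.1404 + 0.2176) = 0.5983.

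- n = 96 (20% of 120 lost), two-sided: (1.4805 − 1.96 × 0.6078)/0.5983 = 0.483, power 68.6%.
- n = 96, one-sided: (1.4805 − 1.645 × 0.6078)/0.5983 = 0.803, power 78.9%.
- n = 120 (no loss), two-sided: (1.6552 − 1.96 × 0.6078)/0.5983 = 0.775, power 78.1%.
- n = 120, one-sided: (1.6552 − 1.645 × 0.6078)/0.5983 = 1.095, power 86.3%.

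An exact calculation for the two-sided chi-square test gives 69.3% at 96 and 78.6% at 120 per arm.

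**Noninferiority, for orientation only.** The text gives no margin, so 5, 10 and 15 points are assumptions. With 96 per arm, one-sided 0.025 and unpooled variance:

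- At the stated rates, power is 90.9% for a 5-point margin and 98.4% for 10 points.
- If both true rates are 68%, power is 11.2% for 5 points, 31.8% for 10 and 60.6% for 15.

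**The case against.** **The β label is a slip that does not drive the number.** The deviate and the 80% in words agree with each other, and 120 is reproduced from them. This stands. The error is in the label, so the needed correction is to state 0.2, not to enlarge the trial to meet 0.1.

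**A reader might infer that the stated power is simply not delivered.** The document does not support that without qualification. Against 80% at one-sided 0.05, which is what the printed deviates target, 96 per arm gives 78.9%. That is essentially 80%. The shortfall appears only against β = 0.1, or against the two-sided test in section 3.7.

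**A reader might infer a definite loss-inflation error.** The formula is not shown and the multiplier is reconstructed. If the multiplier was 1.2, it costs about one point of power (78.9% against 80%).

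**A reader might infer that the inputs were picked to be as favourable as possible.** They were not. The paragraph takes 68%, the midpoint of 65% to 71%. At 65% the same formula gives 2 × 0.74055 × 0.25945 × 2.487² / 0.1811² = 72.5, about 73 per arm.

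**One-sided testing is usual for noninferiority, and the 69% and 78% belong to a test of difference.** Both remarks are fair. With an unstated margin, other combinations also land near 120. A 5-point margin at one-sided 0.025 and 90% power needs 94 per arm, or 118 after dividing by 0.8. But that uses 1.96 and 1.282, not the deviates printed, and section 3.7 as written prescribes a two-sided test of difference. The noninferiority label alone does not reconcile the two sections.

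**96 evaluable per arm is an assumption.** Section 3.4 defines the primary rates over the total number of the group, so excluding those lost is one reading only. The no-loss figures are given for that reason.

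**Conclusion.** The point holds in this form. Section 2.3 contradicts itself on β, and its one-sided α does not match the two-sided test of difference in section 3.7. The figure of 120 per arm corresponds to one-sided 0.05 and 80% power in a margin-free difference calculation at 83.11% against 68%.

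That calculation does not give the 90% implied by β = 0.1, whichever sidedness is used and even with no loss (86% one-sided, 78% two-sided). For the section 3.7 test, power is about 78% with all 120 per arm analysed and about 69% if 20% are lost and excluded.

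These figures assume the stated rates are true and that the test is one of difference. They do not show a shortfall for a noninferiority comparison: with no margin in the text, power for that test cannot be determined.

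**What to change.** Correct the text of section 2.3 as follows:

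1. Replace the β of 0.1 with 0.2, so that the label, the deviate and the 80% agree.
2. State one α and its sidedness, consistent with the primary analysis in section 3.7.
3. Show the allowance for loss as division by (1 − 0.2). With 120 randomised per arm, 20% loss leaves 0.8 × 120 = 96.
4. Restate the delivered power for 120 randomised and 96 evaluable per arm. If the two-sided test of difference stays primary, that is about 69%, or about 78% without loss. If the declared noninferiority comparison is primary, state the margin and give power for that test instead, and align section 3.7 with it.

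The cost is a text correction with no extra patients. If section 3.7 stays as written, the power reported will be less favourable than the paragraph now suggests.

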### Outcomes

3.4

Primary therapeutic outcome: the rate of clinical efficacy and clinical remission at 8 weeks of treatment (last survey point) according to the modified Mayo score (Table 2). Clinical efficacy was defined as a decrease of at least 30% from the baseline and a decrease ≥3 points, with an accompanying decrease in the subscore for bloody stools ≥1 point or absolute bloody stools subscore of 0 to 1. Clinical efficacy rate = effective number / total number of the group ×100%. Clinical remission was defined as a score ≤2, with no individual subscore with a value greater than 1. Clinical remission rate = remission number / total number of the group ×100%.

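### The loss allowance in section 2.3 and the denominator in section 3.4 treat lost patients differently, so the stated 80% certainty does not describe the primary endpoint as literally defined

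*Protocol article*

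**What the plan says.** Section 2.3 (Number of Samples) plans on a mesalazine efficacy rate of about 68%, the middle of a 65% to 71% range, and on this HEC figure: "Our previous study found that the efficacy rates of HEC is 83.11% in treating MAUC". It uses U values of 1.645 and 0.842. On loss it says "The certainty was set at 80%, considering 20% of sample lose", and then "The sample number was set to 120 for each group, 240 in total".

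Section 3.4 (Outcomes) defines the first primary rate as "Clinical efficacy rate = effective number / total number of the group ×100" percent. The remission rate has the same denominator. Both are assessed at week 8 on the modified Mayo score.

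Section 2.2 (Trial design) gives the group sizes: "randomization with a 1:1 allocation ratio in the experimental group (n = 120) or the control group (n = 120".

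Section 3.7 (Data analysis) says that dropouts and excluded cases will be reported. It gives no rule for counting them in the rates, and it tests at two-sided 0.05.

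**The concern.** Adding patients for loss makes sense when lost patients drop out of the comparison and the planning rates hold in those who remain. A rate over the whole group works differently. A patient without a week-8 score cannot meet the definition of efficacy or remission, yet still counts in the denominator. Each loss then lowers the rate in its arm, and equal loss shrinks the difference between arms by the loss fraction. Recruiting 20% more patients does not restore that difference.

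Two things are at stake. First, the 80% may belong to a comparison other than the one the endpoint defines. Second, the trial is declared as noninferiority. If HEC were truly worse, equal loss scored as failure would pull the arms together and make them look more alike than they are. The withdrawal criteria after section 2.5 include lack of improvement and serious adverse events, so some loss may be related to treatment.

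**Working it through.** **Inputs.** P1 = 0.8311, P2 = 0.68, U values 1.645 and 0.842, 20% loss and 120 per arm, all from section 2.3. Whole-group denominator from section 3.4. Two-sided 0.05 from section 3.7. The printed formula is not visible in the text supplied, so the usual pooled form is used, with P = (P1 + P2)/2 as section 2.3 defines it.

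**Step 1: reproduce the plan's figure.** P = (0.8311 + 0.68)/2 = 0.75555.

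n = 2P(1 − P)(1.645 + 0.842)² / (P1 − P2)² = 2 × 0.75555 × 0.24445 × 2.487² / 0.1511² = 100.07.

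100.07 × 1.2 = 120.08, so the stated 120 reproduces. About 100 per arm are meant for the comparison and 20 per arm cover loss.

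**Step 2: apply the section 3.4 denominator.** Assume that the planning rates hold in retained patients, that loss is 20% in each arm, and that a missing score is a non-success.

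- HEC: 0.8 × 0.8311 = 0.665
- Mesalazine: 0.8 × 0.68 = 0.544
- Difference: 0.8 × 0.1511 = 0.121, down from 0.151

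**Step 3: power for a zero-margin difference.** With d the difference in rates and p̄ their mean,

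power = Φ{ [d√n − z√(2p̄(1 − p̄))] / √(p1(1 − p1) + p2(1 − p2)) },

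where z = 1.645 (one-sided, as in section 2.3) or 1.96 (two-sided, as in section 3.7).

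For Step 2 with n = 120 and z = 1.645: [0.12088 × 10.954 − 1.645 × 0.6915] / 0.6862 = 0.272, and Φ(0.272) = 0.607.

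| Reading | n per arm | Rates | One-sided | Two-sided |
|---|---|---|---|---|
| Planning rates in retained patients; only evaluable patients analysed; 20% loss | 96 | 83.1% v 68.0% | 78.9% | 68.6% |
| Planning rates in retained patients; whole-group denominator; 20% loss | 120 | 66.5% v 54.4% | 60.7% | 48.2% |
| Same, 10% loss | 120 | 74.8% v 61.2% | 73.2% | 61.8% |
| Planning rates already count everyone in the group | 120 | 83.1% v 68.0% | 86.3% | 78.1% |

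**Step 4: effect of the denominator alone.** At 20% loss, with rates that hold in retained patients, moving from row 1 to row 2 costs 78.9 − 60.7 = 18.2 points one-sided and 68.6 − 48.2 = 20.4 points two-sided. On the row 2 rates, the Step 1 formula needs about 202 per arm for 80%. That figure only shows the size of the gap and is not a proposal to enrol more.

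**The case against.** **The counting rule may lie elsewhere.** Analysis sets and missing-data rules are commonly left to the SAP or the full protocol. The group total in section 3.4 might mean analysed patients, and the excluded cases in section 3.7 might be patients removed from the analysis. It is true that the document names no analysis set and nowhere says outright that lost patients count as failures, and that absence is not the point here. The point is that two stated items do not fit as worded. The 120 in section 2.2 is the only group size given, and an evaluable-only denominator has to be read into section 3.4.

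**The planning rates may already count everyone.** Section 2.3 calls its inputs efficacy rates, and section 3.4 defines such a rate over the whole group. On that definition nothing is lost: power is about 86% one-sided and the allowance is surplus. This objection stands. The 20% addition suggests rates in retained patients but does not prove it, and the source studies are not at hand.

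**The trial is declared as noninferiority.** All power figures above are for a zero-margin difference. No margin appears in the text shown. With assumed margins, the 66.5% v 54.4% scenario gives one-sided 0.05 power of 86.1% (5 points) or 97.0% (10 points). This also stands: low power for a difference does not establish low power for noninferiority.

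A reader might infer that the trial simply has 61% power on the plan's own rates. The document does not support that. The 66.5% and 54.4% appear nowhere in it and rest on all three assumptions in Step 2.

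**Conclusion.** The inconsistency holds, with its size stated as a range. The sample-size arithmetic reproduces. What fails is the match between the stated certainty and the stated endpoint. With the denominator read literally, power for the planned difference at 120 per arm is about 61% one-sided (48% two-sided) if the planning rates describe retained patients and 20% are lost equally. It is about 73% (62%) at 10% loss, and about 86% (78%) if the rates already count everyone. A figure near the stated 80% arises at 20% loss only if evaluable patients alone are analysed (79% one-sided, 69% two-sided), and section 3.4 would then have to say so.

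None of these figures is power against a noninferiority margin. Three further issues are separate from this point: the mismatch between "β equaling to 0.1" and the U value used, the one-sided against two-sided level, and multiplying by 1.2 rather than dividing by 0.8.

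**What to change.** Enrolment stays at 120 per arm.

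1. In section 3.4, keep the whole-group denominator. State that it is all randomised patients and that a patient without a week-8 modified Mayo score counts as not effective and not in remission.
2. In section 2.3, state whether the 83.11% and the 68% come from everyone treated or from patients who completed.
3. In section 2.3, replace the single 80% with the power at 120 per arm under that denominator, shown by loss rate (for example 10% and 20%) and conditional on the answer to item 2. Label it as power for a difference, not for a noninferiority margin.
4. Do not claim that the 20% addition alone covers loss.
5. Report both primary rates also in patients with a week-8 score, or with multiple imputation of missing scores. This shows how much of any similarity between arms comes from loss scored as failure.

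The cost is some wording in two sections, one extra sensitivity analysis and, under the retained-patient reading, a less favourable stated power. No patients, visits or procedures are added.
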